### Statistical analysis

#### Calculation of sample size

Assuming a median PFS of 7 months and hazard ratio of 0.347 in the IRE arm based on the results of the previous study [24, 25]. This study had one year of enrollment, and the total trial duration was 3 years. The non-inferiority margin is 20%, which was recognized by clinical experts. α and β are the significance level of statistical tests and test power, respectively, α = 0.05 and β = 0.2 in the present study. Considering a dropout rate of 15% during the study, the number of planned patients in each group was 80. Randomization was performed in a 1:1 ratio, with a total of 190 patients enrolled in the two groups.

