**Methods:**

We will conduct a multicenter, randomized, parallel-controlled non-inferiority clinical trial to compare the efficacy and safety of IRE and RFA for hepatocellular carcinoma (HCC). One hundred and ninety patients with HCC from five academic medical centers will be enrolled. The patients will be randomized into treatment arm (IRE) and control arm (RFA). The primary outcome is the progress -free survival (PFS) and the key secondary outcome is the Overall survival (OS).

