### Study outcomes

#### Primary outcome

The primary outcome is to compare the PFS of IRE to RFA for HCC patients.

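### The stated planning inputs, with HR 0.347, do not give 80 patients per group, and 80 is the figure before dropout, not after it

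*Protocol article*

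**What the plan says.** The abstract (Methods) describes a "multicenter, randomized, parallel-controlled non-inferiority clinical trial", and PFS is the primary outcome. The section Calculation of sample size gives these inputs:

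- Effect: "Assuming a median PFS of 7 months and hazard ratio of 0.347 in the IRE arm", attributed to earlier studies.
- Timing: "This study had one year of enrollment, and the total trial duration was 3 years".
- Margin: "The non-inferiority margin is 20%, which was recognized by clinical experts".
- Error rates: "α and β are the significance level of statistical tests and test power, respectively", set to 0.05 and 0.2.
- Size: "Considering a dropout rate of 15% during the study, the number of planned patients in each group was 80", followed by 1:1 randomization and a total of 190.

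**The concern.** A hazard ratio of 0.347 is a reduction in hazard of about 65%. A trial that expects an effect of that size needs few patients, whether it tests superiority or non-inferiority, and 80 per group is several times too many. So either the effect or the number does not belong to the calculation. Two further statements in the paragraph conflict with it: 80 per group does not add up to 190, and β is described as power.

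What is at stake is how the primary result is read. If non-inferiority is not shown, readers need to know how likely that was with equally good treatments. The paragraph implies 80% power but does not show for which effect and margin.

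**Working it through.** **Inputs from the article:** median PFS 7 months, HR 0.347, margin 20%, α 0.05, β 0.2, 12 months of accrual, 36 months in total, 15% dropout, 80 per group, 190 in total.

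**Assumptions made here:** exponential PFS, uniform accrual, and 7 months as the RFA median, so the IRE median is 7/0.347 = 20.2 months. Because the article does not say whether α is one- or two-sided, one-sided 0.025 and one-sided 0.05 are both shown. (z_α + z_β)² is 7.849 and 6.183 respectively.

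**1. Dropout step.** 80/0.85 = 94.1, rounded up to 95, and 95 × 2 = 190. The total follows only if 80 is the number before dropout. If 80 already included dropout, the total would be 160.

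**2. Event probability.** With λ = ln 2/median, P = 1 − [exp(−24λ) − exp(−36λ)]/(12λ). This gives 0.946 at a median of 7 months and 0.641 at 20.2 months, with mean 0.793.

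**3. Attempt to reproduce 80 per group with HR 0.347.** Events = 4(z_α + z_β)²/[ln(margin) − ln(HR)]², and patients per arm = events/(2 × 0.793).

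| Reading | Events (0.025 / 0.05) | Per arm (0.025 / 0.05) |
|---|---|---|
| Superiority (margin 1) | 28.0 / 22.1 | 17.7 / 13.9 |
| Non-inferiority, HR margin 1.2 | 20.4 / 16.1 | 12.9 / 10.1 |
| Non-inferiority, HR margin 1.25 (= 1/0.8) | 19.1 / 15.1 | 12.0 / 9.5 |
| Stricter margin, HR 0.8 | 45.0 / 35.4 | 28.4 / 22.3 |

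For a 20-point margin on the PFS rate, n = (z_α + z_β)²[p₁(1 − p₁) + p₂(1 − p₂)]/(0.20 + p₂ − p₁)², with p₁ for RFA and p₂ = p₁^0.347 for IRE:

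- At 7 months (0.500 against 0.786): 13.9 / 10.9 per arm.
- At 12 months (0.305 against 0.662): 11.0 / 8.7 per arm.

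All these readings lie between about 9 and 28 per arm. Adding 15% dropout to the largest gives 28.4/0.85 = 33.4. Taking 7 months as the IRE median lowers the hazard-ratio rows further. None comes near 80.

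**4. Power of 160 evaluable patients at HR 0.347.** Events = 160 × 0.793 ≈ 127, and √127/2 ≈ 5.63. At one-sided 0.025:

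- Superiority: 5.63 × 1.058 − 1.960 = 4.00, power above 99.9%.
- HR margin 1.2: 5.63 × 1.241 − 1.960 = 5.03, power above 99.9%.
- HR margin 0.8: 5.63 × 0.835 − 1.960 = 2.74, power 99.7%.

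**5. Power of 160 evaluable patients if the arms are equal.** Events = 160 × 0.946 ≈ 151, and √151/2 ≈ 6.15.

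- HR margin 1.2: 6.15 × 0.182 = 1.12. Power is 20% (one-sided 0.025) or 30% (0.05).
- HR margin 1.25: 6.15 × 0.223 = 1.37. Power is 28% or 39%.
- 20 points at 7 months: 0.20/√(2 × 0.25/80) = 2.53. Power is 72% or 81%.
- 20 points at 12 months: 0.20/√(2 × 0.305 × 0.695/80) = 2.75. Power is 78% or 87%.

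**6. Readings that do give about 80.** Both set HR 0.347 aside and assume equal arms with one-sided 0.05.

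- 20 points at 7 months: 6.183 × 0.50/0.04 = 77.3, so 78 per arm. At one-sided 0.025 the same reading needs 99.
- HR margin 1.5: 150.4 events, 79.5 per arm. The value 1.5 appears nowhere in the article.

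**The case against.** The strongest reply is that one reading comes close to the planned number: equal arms, a 20-point margin at 7 months and one-sided 0.05 need 78 per arm, and 80 per arm give 81% power. It uses the stated 7 months, 20%, 0.05 and 0.2. This may be how 80 was obtained. But it drops HR 0.347, and it relies on equality and a one-sided test that the article does not state. It supports the view that the printed effect is not the basis of the number.

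Three stronger readings are tempting, and the article does not support them.

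- *The trial was sized on HR 0.347.* The article states that value as its assumption, but step 3 shows that the number cannot have come from it.
- *The trial lacks power and will probably fail to show non-inferiority.* The 20% to 39% figures hold only if 20% is a hazard-ratio margin of 1.2 or 1.25. On a percentage-point scale, power under equality is 72% to 87%.
- *A non-inferiority trial must be planned at HR = 1.* A favourable planning effect is not an error in itself, and the sources cited for this one are not at hand.

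It is also fair to say that a journal article commonly leaves the formula, the event target and the sidedness of α to the full protocol or analysis plan. Their absence is not part of this point. The point rests on figures the article prints, and a fuller document could not make HR 0.347 yield 80 per arm, or twice 80 equal 190. The β wording is a minor labelling slip: 0.2 is plainly the type II error.

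**Conclusion.** The sample-size basis is wrong as printed. With HR 0.347 the requirement is about 9 to 28 per arm, roughly a ninth to a third of the stated 80, and the implied 80% power is not the power at that effect. This does not depend on the scale of the margin or the sidedness of α. It rests on exponential PFS, uniform accrual and 7 months as the RFA median; taking 7 months as the IRE median does not rescue it.

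What power the trial has if the treatments are equal cannot be settled from the article. It ranges from 20% to 87% over the readings in step 5, and the margin's scale drives most of that range. The dropout and β errors need no assumptions.

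**What to change.** Keep enrolment at 190 and rewrite the paragraph:

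- Replace HR 0.347 with the planning assumption that was actually used to obtain 80 per group.
- State the scale of the clinically agreed 20% margin and the one-sided α that goes with it. If it is a PFS-rate difference, give the time point.
- Restate the power that 160 evaluable patients give for that margin, at the planning effect and at HR = 1.
- Correct the counts to 80 per group before and 95 per group after 15% dropout, and the error rates to β = 0.2 (power 80%).

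Do not derive a new margin from the available number of patients. Values such as 1.5 can be solved backwards from the sample size, but they have no clinical basis in the article.

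The cost is wording in the protocol and the analysis plan. The downside is that the stated power may become less favourable. When the article was written, 48 of 190 patients had been recruited and no PFS or OS endpoint had been observed, so a correction at that stage could not have been influenced by outcomes.

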## Preliminary results

### Basic characteristics

At the time of this writing, 48 (25.3%) patients had been recruited from 5 centers, of which, 33 patients with 38 tumors had completed the 1-month follow-up and 21 patients have complete the 3-month follow up, with 2.3 months median follow up period. Their basic information is shown in Suppl. Table 2. The patients’ median age was 59.1 years (55.8 years in the Irreversible electroporation (IRE) group and 63 years in the RFA group), and their ages ranged from 29 to 79 years. Seventeen patients have cirrhosis. Only one patient has Child–Pugh grade B disease. The mean longest diameter of the 38 tumors was 1.9 cm and the mean largest tumor diameter is 3.9 cm (Suppl. Table 3).

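### The 80 per group is worded as already allowing for 15% dropout, but the stated total of 190 at 1:1 means 95 per group; 80 fits only as the number before dropout.

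*Protocol article*

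**What the plan says.** The per-group number and the total stand in consecutive sentences of the protocol article, under Calculation of sample size. The first is "Considering a dropout rate of 15% during the study, the number of planned patients in each group was 80". The second is "Randomization was performed in a 1:1 ratio, with a total of 190 patients enrolled in the two groups".

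The total is the same elsewhere. The abstract (Methods) states "One hundred and ninety patients with HCC from five academic medical centers will be enrolled". Under Basic characteristics, progress is given as "48 (25.3%) patients had been recruited from 5 centers", and the Discussion repeats this percentage. No other per-group sample size is printed.

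**The concern.** As worded, 80 is the planned size of each group with dropout already taken into account. At 1:1 that implies 160 patients, which cannot stand beside a total of 190. One of the two sentences must be wrong or mislabelled.

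The per-group number is what a randomisation list, a site quota or a later report would take from this paragraph, and 80 is the only such number the article offers. Anyone who used it in the belief that dropout was covered would have no allowance at all. When the article was written, only about a quarter of the planned patients had been recruited, so a clear per-group target still mattered.

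**Working it through.** **Inputs, all from the protocol article**
- Per-group number 80, dropout 15%, allocation 1:1, total 190 (Calculation of sample size).
- Total 190 (abstract, Methods).
- 48 recruited, given as 25.3% (Basic characteristics; Discussion).

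**1. Reproduce the stated total, with 80 as the number before dropout.**
Number to randomise = evaluable number / (1 − dropout) = 80 / 0.85 = 94.1, rounded up to 95 per group. Then 2 × 95 = 190, an exact match. Check: 95 × 0.85 = 80.75, so at least 80 remain evaluable, whereas 94 × 0.85 = 79.9 falls just short.

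**2. Try the other readings.**
- 80 already includes dropout, as worded: 2 × 80 = 160, not 190.
- 80 inflated by multiplication: 80 × 1.15 = 92 per group, 184 in total, not 190.

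**3. Find the denominator behind the recruitment percentage.**
48 / 190 = 25.3%, as printed. 48 / 160 = 30.0%, which is not.

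**4. Size of the misstatement.**
95 − 80 = 15 per group, or 190 − 160 = 30 patients over both groups.

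**5. What follows if someone did enrol 80 per group.**
80 × 0.85 = 68 evaluable per group, compared with 80.75 when 95 per group are randomised.

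**The case against.** The strongest reply is that nothing is really in doubt. The number 160 is printed nowhere, every stated total or denominator is 190, and halving 190 gives 95 at once. On this view the sentence is loosely worded, and the dropout allowance is intact at the planned enrolment. Most of that stands. A reader might infer that the plan sets two rival enrolment targets, 160 and 190. It does not: 160 comes only from doubling the misplaced 80.

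A reader might also infer a loss of power. If 80 evaluable per group gave exactly 80% power, 68 would give Φ[(z_α + z_0.80) × √(68/80) − z_α], which is 73.3% at one-sided 0.025 and 74.1% at one-sided 0.05. The article does not support that as a consequence of the plan, for three reasons.
- Nobody plans to enrol 160.
- The stated inputs do not show that 80 gives 80% power. Suppose the 20% margin means a hazard ratio of 1.20 (the scale is not stated), with exponential progression-free survival, a 7-month median on RFA, 12 months of accrual and 36 months in total. At a true hazard ratio of 0.347, about 11 to 13 patients per group suffice, so 68 instead of 80 costs essentially nothing. At a true hazard ratio of 1, about 393 (one-sided 0.05) to 500 (one-sided 0.025) per group are needed, so neither 68 nor 80 comes close.
- Patients who drop out of a Kaplan-Meier analysis are normally censored and contribute until then, so removing 15% of them outright overstates the loss.

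One further point can be made for the printed wording: 68 / 0.85 = 80 exactly, so 80 could be an inflated figure built on a base of 68. But 68 appears nowhere in the article, and this reading leaves 190 unexplained.

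What the reply does not remove is that the sentence is wrong as it stands. Because the design inputs do not lead to 80, a reader can find the intended meaning only by working backwards from 190.

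**Conclusion.** The point holds as an error in a stated sample-size figure. The 15% allowance is attached to 80, the number before inflation, and the per-group number to randomise is understated by 15 (80 instead of 95). The total of 190 is consistent throughout and is unchanged. If 190 are enrolled, this error costs no patients and no power. The fall to about 68 evaluable per group is conditional on someone enrolling to the printed 80.

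The conclusion assumes that 190 is the intended total, which every statement of the total in the article supports, and that the allowance was made by dividing by 0.85, the only method tried that returns 190 from 80. It says nothing about whether 80 is an adequate base number. That is a separate question, which this correction leaves open.

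**What to change.** Replace the per-group sentence under Calculation of sample size with: *80 evaluable patients per group are required; allowing for 15% dropout (80/0.85 = 94.1), 95 patients per group, 190 in total, will be randomised 1:1.* Use 95 per group as the target for enrolment and for the randomisation list. The sponsor should confirm against the underlying calculation that 80 is the number before dropout.

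The cost is one corrected sentence. No patients are added, because 190 is already the stated total, and no design feature or analysis changes.

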#### Statistical methods

The statistical description will be performed using the mean, standard deviation, maximum, minimum, median, confidence interval, and rate (composition ratio). For measurement data conforming to a normal or approximately normal distribution, the t-test for two independent samples, repeated-measures analysis of variance, and analysis of covariance will be used for comparison between the two groups, and the paired t-test will be used for comparison between the pretreatment period and each follow-up time point. When the distribution does not conform to a normal or approximately normal distribution, the Wilcoxon rank sum test will be used for comparison between the two groups, and the paired Wilcoxon rank sum test will be used for comparison between the pretreatment period and each follow-up time point. Categorical data will be compared between the two groups using the chi-square test and Fisher’s exact test. McNamar’s chi-square test will be used for comparison between the pretreatment period and each follow-up time point, and the Cochran–Mantel–Haenszel chi-square test will be used for the central effect. The Wilcoxon rank sum test will be used to compare the rank data between the groups. PFS and OS were summarized with the Kaplan-Meier method. mixed-effects Cox models will be used to analyze factors affecting the efficacy. PFS will be based on BICR assessments of tumor assessment and using mRECIST version 1.1. In our final analysis, we will perform the analysis based on intention to treat, full analysis set, Per-Protocol and Safety Analysis Population analysis set. See Supplementary Materials for detailed analysis sets. Analyses were done using R version 4.2.3, an open-source software developed initially in 1993 by Ross Ihaka and Robert Gentleman at the University of Auckland, New Zealand.

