### Patient screening

Eligibility screening will be performed within 14 days before procedure, as shown in Table 1 & Suppl. Table 1.

**Table 1 Tab1:** Follow-up scheme

Trial phase Trial content			a Screening	Follow-up			
			Visit 1	Visit 2	Visit 3	Visit 4	Visit 5
			Preoperative (-14 ~ 0d)	Ablation day (0d)	2 ± 1d after first ablation	30 ± 5d after first ablation	Every 3 months after first ablation
Informed consent^b^			√				
Demographic data			√				
History of liver tumors and past medical history			√				
Vital signs			√	√	√	√	√
Laboratory examination	Urine pregnancy^c^		√				
	Routine urine test^d^		√				
	Routine blood test^e^		√		√	√	√
	Stool routine examination^f^		√				
	Hepatorenal function^g^		√		√	√	√
	Serum electrolyte^h^		√		√	√	√
	Coagulation function^i^		√		√	√	√
	Myocardial enzyme^j^		√		√	√	√
	Tumor marker^k^		√			√	√
Lung CT scan			√				
ECG			√		√	√	√
CEUS			√		√	√	√
Enhanced MRI/CT examination of upper abdomen^l^			√			√	√
ECOG			√			√	√
Child-Pugh			√			√	√
Random allocation				√			
Ablation				√			
Observation of device defects				√			
Evaluation of ablation efficacy						√	√
Record combined medication/treatment			√	√	√	√	√
Handle and record adverse events				√	√	√	√
Verify deviation from protocol				√	√	√	√
Immune index in peripheral blood		The proportion of MDSC ^o^	√	√	√	√	√
		The proportion of TEMs ^o^	√	√	√	√	√
		The concentration of cytokines in serum ^o^	√	√	√	√	√
		Tregs^p^	√	√	√	√	√
		aTregs^r^	√	√	√	√	√
		rTregs^s^	√	√	√	√	√

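### The plan does not say which listed method applies to the repeated laboratory and immune measures; one baseline-adjusted mixed model on all available visits should replace the t-test and repeated-measures ANOVA (low severity)

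*Protocol article*

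**What the plan says.** The Statistical methods section assigns methods by type of data, not by variable. Between arms, for measurement data that are at least approximately normal, "the t-test for two independent samples, repeated-measures analysis of variance, and analysis of covariance will be used for comparison between the two groups". Within an arm, "the paired t-test will be used for comparison between the pretreatment period and each follow-up time point". If the data are not normal, "the Wilcoxon rank sum test will be used for comparison between the two groups", with a paired rank test within each arm.

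Table 1 (Patient screening) schedules blood count, liver and kidney function, electrolytes, coagulation and myocardial enzymes at screening, about day 2, about day 30 and then "Every 3 months after first ablation". The rows under "Immune index in peripheral blood" are ticked at all five visit columns. No last visit is given for these measures, and the text does not say which visits a repeated-measures analysis would span.

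The only planned loss figure is in Calculation of sample size: "Considering a dropout rate of 15% during the study". On analysis sets, the article says "See Supplementary Materials for detailed analysis sets"; that supplement was not available for this review.

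**The concern.** The three between-arm methods treat gaps and baseline differently, so the choice among them matters.

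- **Classical repeated-measures ANOVA** needs a full set of visits from each patient and deletes anyone with a gap in its window. With an open-ended quarterly schedule the window could be long. If dropout is related to outcome, those who remain are a selected group and no longer the randomised arms.
- **A two-sample t-test at one visit** keeps everyone measured at that visit. If it is run on the values themselves, it ignores baseline, and each visit is tested on a somewhat different set of patients. The article does not say whether values or changes are compared.
- **ANCOVA** can adjust for baseline, but the article does not tie it to these measures.

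At stake are the precision and clarity of the arm comparisons of liver enzymes, CK-MB and immune indices. The preliminary results show the practical side. The Hepatorenal function section gives separate before-after P-values for each arm, and the Discussion then says that the two treatments' effects did not differ significantly at one month. The article text gives no between-arm estimate or interval, and two within-arm P-values do not supply one.

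**Working it through.** **1. The plan's own figure.** Inputs from Calculation of sample size: 80 per arm, 15% dropout, 190 in total. 80 / (1 − 0.15) = 94.1, so 95 per arm and 190 in total. This reproduces the stated total, so 15% is the loss the plan allows for.

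**2. Visits.** From Table 1: day 2, day 30 and months 3, 6, …, 24, which is 2 + 8 = 10 follow-up visits to month 24. The ablation-day immune sample is left out. So is the 60-day visit, which the Follow-up section names but Table 1 as shown does not.

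**3. Are any of these visits out of reach?** With one year of enrolment and three years in total, the last patient has 36 − 12 = 24 months of potential follow-up. On the planned calendar, every visit to month 24 can be reached.

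**4. Loss from dropout alone, complete cases only.** If all 15% have gone by month 24, the loss is 15%, about 28 of 190. If dropout runs at a constant rate over 36 months, the share remaining at month t is 0.85^(t/36):

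| Window to month | Complete | Lost |
|---|---|---|
| 1 | 0.85^(1/36) = 0.995 | 0.5% |
| 3 | 0.85^(3/36) = 0.987 | 1.3% |
| 12 | 0.85^(12/36) = 0.947 | 5.3% |
| 24 | 0.85^(24/36) = 0.897 | 10.3% |

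Under the same constant rate, a model using all available data loses 4.3% of the scheduled values to month 24 (baseline counted), against 10.3% of patients.

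**5. Adding missed visits.** The documents give no missed-visit rate, so 2% to 5% per visit, independent across visits, is an assumption. With the full 15% dropout and 10 visits, the complete share is 0.85 × (1 − q)^10:

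| q (assumed) | Complete | Lost |
|---|---|---|
| 2% | 0.85 × 0.98^10 = 0.69 | 31% |
| 3% | 0.85 × 0.97^10 = 0.63 | 37% |
| 5% | 0.85 × 0.95^10 = 0.51 | 49% |

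A loss of one third needs q = 1 − ((2/3)/0.85)^(1/10) = 2.4%.

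**6. A short window.** The one laboratory analysis shown uses baseline, day 2 and day 30, so two follow-up visits. Even if the whole 15% is charged by day 30, the complete share is 0.85 × 0.98² = 0.82 to 0.85 × 0.95² = 0.77. If dropout instead builds at a constant rate to 15% at month 24, 0.85^(1/24) = 0.993 remain at month 1. The complete share is then 0.993 × 0.98² = 0.954 to 0.993 × 0.95² = 0.896, a loss of about 5% to 10%.

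**The case against.** Much of the case on the other side stands.

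- **Not every listed method deletes patients.** A reader might infer that the t-tests share this fault. They do not: per-visit t-tests, Wilcoxon tests and ANCOVA lose no one for a gap at another visit.
- **ANCOVA is in the same sentence.** The plan therefore does not rule out baseline adjustment. It leaves open whether these measures would get it.
- **Skewed enzymes would go to Wilcoxon tests.** If ALT, AST and CK-MB are not approximately normal, the plan's own rule takes them away from repeated-measures ANOVA. The deletion problem then does not arise for them. What remains is a rank test without baseline adjustment.
- **The large losses need a long window.** Nothing says that the ANOVA spans all 10 visits.
- **The preliminary counts are not lost data.** The article reports that "33 patients with 38 tumors had completed the 1-month follow-up and 21 patients have complete the 3-month follow up", and a reader might take 21/33 = 64% as the share an ANOVA would keep. It is a snapshot at the time of writing, with 2.3 months' median follow-up, and shows how far follow-up had got. The article reports no missed visits.
- **Details can wait for the analysis plan.** This is fair for the visit window, covariance structure and missing-data rules. It does not fully answer the point, because the article does name methods for this kind of data, and a better one is available at little cost.

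**Conclusion.** The point holds as a low-severity improvement. The plan lists t-tests, repeated-measures ANOVA and ANCOVA without assigning one to the repeated laboratory and immune measures. Of the first two, one deletes incomplete patients and the other, run on visit values, ignores baseline.

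On the plan's own 15%, the complete-case loss is at most 15% to month 24, and about 10% if dropout is even over 36 months. The 31% to 49% range rests on assumed missed-visit rates of 2% to 5% on top of the full 15%, and on an assumed 10-visit window. A reader might infer that a third or more of the data will be lost. The documents do not support that as an expectation: they state no missed-visit rate and no window, and no visit to month 24 is out of reach on the planned calendar. These figures count dropout and missed visits only; losses through death, if not already within the 15%, are not included.

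A reader might also infer a threat to the trial's main conclusion. There is none from this source. The listed outcomes are PFS, OS, ablation rates, adverse events, response rate and duration of response. The laboratory and immune measures are not among them, except where a laboratory value is recorded as an adverse event.

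**What to change.** For the repeated continuous laboratory and immune measures, replace the t-test and repeated-measures ANOVA with one mixed model for repeated measures per variable:

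- **Terms:** baseline value, arm, visit and arm-by-visit, with skewed enzymes on the log scale.
- **Data:** all available visits of all randomised patients, with the visit window stated.
- **Reporting:** arm differences with 95% confidence intervals at day 2 and day 30; later visits descriptively.

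The covariance structure can be left to the statistical analysis plan. The model keeps patients with gaps and is valid if missingness depends only on data already observed, which should be stated as its assumption. The cost is a change of wording and slightly more analysis work in R, the software already chosen. No new data are needed, and the PFS analysis does not change.
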